# Evaluation of the efficacy and safety of *Escherichia coli*-derived recombinant human bone morphogenetic protein-2 in transforaminal lumbar interbody fusion to treat degenerative spinal disease: a protocol of prospective, randomized controlled, assessor-blinded, open-label, multicenter trial

**DOI:** 10.1186/s13018-022-03289-w

**Published:** 2022-08-31

**Keywords:** Degenerative lumbar disorders, Recombinant human bone morphogenetic protein-2, Transforaminal lumbar interbody fusion, Randomized controlled trial

## Abstract

**Background:**

Recombinant human bone morphogenetic protein-2 (rhBMP-2) has been widely used as an alternative bone graft in spine fusion surgery. However, clinical outcome such as effects and complications has not yet been revealed for transforaminal lumbar interbody fusion (TLIF). Although previous studies have reported some results, the evidence is weak. Therefore, the purpose of this trial is to evaluate the effectiveness and safety of *Escherichia coli*-derived rhBMP-2 combined with hydroxyapatite (HA) in TLIF.

**Methods:**

This trial is designed as a prospective, assessor-blinded, open-label, multicenter, randomized controlled study. Participants will be recruited from six tertiary teaching hospitals. All randomized participants will be undergoing one- or two-level TLIF with rhBMP-2 (77 participants) as the active experimental group or with an auto-iliac bone graft (77 participants) as the control group. The primary interbody fusion rate outcome will be evaluated using computed tomography (CT) 12 months after surgery. The secondary outcomes will be as follows: clinical outcomes (visual analog scale score, EuroQol-5-dimensions-5-level score, Oswestry Disability Index score, and some surgery-related variables) and adverse effects (radiculitis, heterotrophic ossification, endplate resorption, and osteolysis). Radiological outcomes will be evaluated using simple radiography or CT. All outcomes will be measured, collected, and evaluated before surgery and at 12, 24, and 52 weeks postoperatively.

**Discussion:**

This study will be the primary of its kind to evaluate the effectiveness and safety of *E. coli*-derived rhBMP-2 with HA in one- or two-level TLIF. It is designed to evaluate the equivalence of the results between rhBMP-2 with HA and auto-iliac bone graft using an appropriate sample size, assessor-blinded analyses, and prospective registration to avoid bias. This study will set up clear conclusions for using *E. coli*-derived rhBMP-2 with HA in TLIF.

*Trial registration*: This study protocol was registered at Korea Clinical Research Information Service (https://cris.nih.go.kr; number identifier: KCT0005610) on 19 November 2020. And protocol version is v1.1, January 2022.

## Background

After the discovery of bone morphogenetic proteins by Marshall Urist in 1965 [1], the frequency of osteoinductive growth factor use in spinal surgery has significantly increased [2–5]. The use of recombinant human bone morphogenetic protein-2 (rhBMP-2) during lumbar fusion surgery as an alternative to autogenous bone graft can minimize complications, such as pain at the donor site, and it has been confirmed that it has the same effect as autologous long bone during spinal fusion [6, 7]. When rhBMP-2 was used in anterior lumbar interbody fusion (ALIF) and lateral lumbar interbody fusion (LLIF), high fusion rates were observed, respectively (94.5% and 92%) [8, 9]. Furthermore, the union rate of the transforaminal lumbar interbody fusion (TLIF) treated with rhBMP-2 was 96.6%, which was higher than that of the non-rhBMP-2 group (92.5%) [10, 11]. Therefore, rhBMP-2 may be a good substitute for bone fusion, which could be used to reduce iliac bone graft donor site morbidity [6]. Despite its high osteoinductivity, rhBMP-2 is difficult to apply clinically because it is extracted from mammals and expensive. However, *Escherichia coli*-derived rhBMP-2 shows a better extraction rate than that of mammals, and high osteogenic activity and cost-effectiveness have been reported [12, 13].

There is still no clear evidence on the clinical and radiographic efficacy and safety of *Escherichia coli*-derived rhBMP-2 on TLIF surgery. Therefore, a randomized controlled trial (RCT) is considered necessary. Specifically, we will compare the safety of using *E. coli*-derived rhBMP-2 with hydroxyapatite (HA) or autogenous iliac bones in patients in need of TLIF to complement the limitations of previous studies and confirm whether the *E. coli*-derived rhBMP-2 with HA bone union rate is non-inferior to that of autogenous iliac bone, as well as its clinical efficacy and safety.

## Methods

### Ethics statements

The design and protocol of this trial were approved by the institutional review board (IRB) of our hospitals (IRB number: B-2008-630-003). Contrary to this trial plan, any changes that could affect future research data will be approved by the research ethics committee before conducting. Informed consent will be obtained from all participants. The results will be submitted to peer-reviewed publications.

### Trial design and participants

In this multicenter, assessor-blinded, open-label, prospective RCT, a total of 154 adults (age, 19–80 years) who will be undergoing TLIF for degenerative lumbar disease will be recruited from six tertiary teaching hospitals to evaluate the efficacy and safety of *E. coli*-derived rhBMP-2 combined with HA in TLIF. Participants will visit the hospital at 12, 24, and 52 weeks postoperatively, so we can evaluate their outcomes. Eligibility for enrollment is based on the following inclusion and exclusion criteria (Table 1, Fig. 1).

**Table 1 Tab1:** Inclusion and exclusion criteria

Inclusion criteria
Age 19–80 years
Patients needing TLIF and posterior pedicle screw fixation at one or two levels between L1 and S1 because of one of the following degenerative lumbar diseases (including patients who do not respond despite 3 months of non-surgical treatment or who have persistent pain with a VAS score ≥ 4):
Lumbar spinal stenosis
Severe herniated intervertebral disk requiring wide laminectomy
Spondylolisthesis or spondylolysis
Recurrent herniated intervertebral disk
Patients able to understand and consent to the study
Patients willing to participate and comply with our proposed follow-up protocol

Exclusion criteria
History of lumbar fusion surgery at the same level
Pregnant, lactating, or childbearing-age patients who do not agree to maintain contraception during the clinical period
Patients with severe osteoporosis (lumbar T-score < − 3.0)
History of malignancy (but patients can participate if the disease has not been relapsed within the last 5 years after being cured)
Hypersensitivity to rhBMP-2, HA, or the PEEK cage
Patients with any of the following diseases that make it difficult to proceed with the protocol (e.g., psychological disorders, drug abuse, abnormal liver, kidney, heart, respiratory function, infectious disease, metabolic disease, ankylosing spondylitis, tumor, trauma, etc.)
Patients taking the parathyroid hormone or bisphosphonate for osteoporosis
Patients with autoimmune disease who need to take high-dose steroids for a long time
Patients who smoke > 20 cigarettes a day
Body mass index > 35 kg/m^2^
Patients who cannot stop taking antithrombotic drugs or anticoagulants before surgery and are expected to have bleeding during surgery
Severe diabetic mellitus patients with complications
A person whose life expectancy is judged to be short (terminal patient)
Patients unable to understand and consent to the protocol

*TLIF* transforaminal lumbar interbody fusion; *VAS* visual analog scale; *rhBMP-2* recombinant human bone morphogenetic protein-2; *HA* hydroxyapatite; *PEEK* polyetheretherketone

**Fig. 1 Fig1:**
[figure not shown]
CONSORT study flow diagram of this study protocol

### Recruitment

Participants will be recruited if they are going to receive TLIF for lumbar degenerative disease at one or two levels in six hospitals. A blinded assessor will conduct the baseline screening to include participants. All participants will choose to participate in the trial after receiving an oral explanation by the evaluators and providing written informed consent of the same content. No monetary benefit will be given to the participants, and no added harm or adverse events are anticipated over traditional instrumented fusion surgery.

### Randomization

The included participants will be randomly assigned to two groups at a 1:1 ratio: an active rhBMP-2 group and a control auto-iliac bone group, following a computer-generated randomization list prepared by a researcher. This lists will be integrated into a web-based eCRF platform that is accessible to researchers who had qualified at this study. This process will be implemented independently for each of the six hospitals, and the surgeon will be notified of the results immediately before surgery.

Participants randomized to the active *E. coli*-derived rhBMP-2 group will be treated with *E. coli*-derived rhBMP-2 and HA during TLIF. The dose of *E. coli*-derived rhBMP-2 at each segment will be 0.5–1.0 mg, and the maximum dose for one participants will be 2.0 mg. Participants randomized to the control auto-iliac bone group will receive autogenous iliac bone from the posterior iliac crest.

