##### Clinical outcomes

Patient-reported outcomes, which includes the Oswestry Disability Index (ODI) score for lumbar disabilities, EuroQol-5-dimensions-5-level (EQ-5D-5L) value for overall quality of life, and VAS pain scores, will be collected before surgery and AT 12, 24, and 52 weeks postoperatively. Safety will be assessed by evaluating adverse events and effects which is related to surgery. Adverse events and surgery-related effects will be made report to the appropriate institution. Laboratory tests for the rhBMP-2 antibody will be performed before surgery and at 12 weeks after surgery. These results and data will be compiled by a blinded assessor and enrolled using the eCRF system (Table 2).

**Table 2 Tab2:** Evaluation schedule

Visit type	Screening	Operation	Follow-up		
Visit	1	2	3	4	5
Visit week	− 4 ~ 0 weeks	0 ~ 2 days	12 weeks	24 weeks	52 weeks
			± 5 weeks	± 8 weeks	± 8 weeks
Trial description and consent	○				
Demographic data^a^	○				
Physical examination	○				
Vital sign	○				
Laboratory test^b^	○				
Bone mineral density	○				
Sampling for rhBMP-2 antibodies^c^	○		○		
Inclusion/Exclusion criteria	○	○			
Randomization		○			
Operation		○			
Simple radiographs	○				
Computed tomography					○
ODI	○		○	○	○
EuroQol-5-dimensions	○		○	○	○
VAS	○		○	○	○
Union rate evaluation^d^					○
Concomitant drug		○	○	○	○
Adverse events		○	○	○	○

*rhBMP-2* recombinant human bone morphogenetic protein-2; *ODI* Oswestry Disability Index; and *VAS* visual analog scale

^a^Baseline patient characteristic, including past medical/surgical history, physical examination

^b^including CBC, chemistry, urinalysis, urine HCG test

^c^Test for BMP-2 antibody baseline. Applicable only to the rhBMP-2 control group after surgery

^d^Evaluation in simple radiographs and CT by 2 independent orthopedic specialists who do not participate in this study process

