### Sample size

This clinical study will compare the interbody fusion rate between the two groups at 52 weeks after surgery and determine whether *E. coli*-derived rhBMP-2 with HA is non-inferior to auto-iliac bone graft in TLIF. According to a previous report, the interbody bone union rate was 92.7% on CT at 12 months postoperatively [14]. For the primary outcome analysis, we calculated that a sample size of 154 participants would provide at least 90% power to show the non-inferiority of rhBMP-2 with HA graft to autogenous iliac bone graft with a one-sided alpha value of 0.05 and a non-inferiority margin of 10% for the 12-month fusion rate of TLIF with the PEEK cage, assuming a 15% dropout rate at 12 months. The sample size was calculated by Power Analysis and Sample Size software, version 15 (NCSS, Kaysville, UT, USA). Therefore, this trial will recruit 154 participants to confirm the equivalence between the rhBMP-2 active group and auto-iliac bone graft control group in TLIF.

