### Statistical analysis

Modified intention-to-treat (mITT) and per-protocol (PP) analyses will be conducted. The primary outcome will be analyzed using the PP strategy. The interbody fusion rate at 12 months after surgery in the rhBMP-2 group will be considered non-inferior to that in the auto-iliac graft group if the lower limit of the 95% confidence section of the fusion rate in the rhBMP-2 group is limited to within the non-inferiority margin of 10%. The mITT strategy will be the principle analysis for secondary outcomes, and we will analyze whether participants received a randomized graft material to reduce the effects of crossover and drop out that could disable the randomization of both groups assigned.

To evaluate the randomized graft material effect on clinical outcomes (i.e., ODI, EQ-5D-5L, and VAS pain scores), a linear repeated-measures mixture model is going to be used. Other radiographic and clinical outcomes and side effects between the two groups will be analyzed used by the chi-square test for categorical variables and the Student’s t test for continuous variables.

All statistical analyses will be performed using Stata/MP 17.0 (StataCorp LLC, College Station, TX). Statistical significance will be defined as a two-sided *p* value < 0.05, except for the *p* value from the non-inferiority test, which was one-sided.

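### Allocation is run separately in each of six hospitals, but the tests named for the remaining secondary outcomes have no hospital term and hospital is not mentioned elsewhere in the analysis; the cost is modest precision, not bias

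*Protocol article*

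**What the plan says.** **Allocation.** Under Randomization, participants are "randomly assigned to two groups at a 1:1 ratio", and "This process will be implemented independently for each of the six hospitals". The article does not say whether the lists are blocked within hospital.

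**Primary outcome.** Under Statistical analysis, a 95% confidence limit for 12-month fusion is held against the 10% margin. No interval method is named and hospital is not mentioned.

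**Clinical scores.** For ODI, EQ-5D-5L and VAS, "a linear repeated-measures mixture model is going to be used". Its terms are not listed. Under Clinical outcomes, the same scores "will be collected before surgery and AT 12, 24, and 52 weeks postoperatively".

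**All other outcomes.** These "will be analyzed used by the chi-square test for categorical variables", with Student's t test for continuous ones. Neither test has a hospital term.

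**The concern.** Running allocation separately by hospital is stratification by hospital, so the analysis should normally use the same strata. Fusion, pain and disability can plausibly differ between hospitals: the trial admits one- or two-level surgery for several diagnoses, and the control graft volume may vary from 5 to 10 cc per segment. That they do differ is an assumption. When they do, an analysis that ignores hospital leaves between-hospital variation in the error term.

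The chi-square and t tests are named choices, so an analysis plan that followed the article would run them unstratified. They cover the adverse-effect comparisons, and safety is a declared aim. Precision is at stake, in a trial whose primary comparison has none to spare. The same question arises for the pre-operative scores, which are strong candidates for reducing error in the clinical-score model if they are used.

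**Working it through.** **Inputs from the protocol article.** Six hospitals; 1:1 allocation; 77 per arm; fusion rate 92.7%; margin 10 points; one-sided alpha 0.05; power 90%; dropout 15%, so 77 × 0.85 ≈ 65 evaluable per arm. Equal rates in the two arms is an assumption, because only one rate is given.

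**Assumed, because the article gives no figure.** Share of outcome variance explained by hospital, h = 1% to 10%; correlation of baseline with follow-up score, ρ = 0.3 to 0.5.

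**Step 1: the stated sample size.** The article says that "a sample size of 154 participants would provide at least 90% power".
- n per arm = (1.645 + 1.282)² × 2 × 0.927 × 0.073 / 0.10² = 116
- after dropout: 116 / 0.85 = 137 per arm, 274 in total

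The stated 154 is not reproduced under equal rates. A figure near 77 per arm appears only with a higher rate in the rhBMP-2 arm, for example 95% against 92.7% (66, or 78 with dropout), which the article does not state. At 65 per arm:
- SE = √(2 × 0.927 × 0.073 / 65) = 0.0456
- power = Φ(0.10 / 0.0456 − 1.645) = 70.8%

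**Step 2: hospital in the fusion comparison.** Analysing by hospital multiplies the variance by about (1 − h). This ignores any small loss from unequal arms within a hospital. The implied SD of hospital fusion rates is √(h × 0.927 × 0.073).

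| h | SD of hospital rates | SE | Power |
|---|---|---|---|
| 0 | – | 0.0456 | 70.8% |
| 1% | 2.6 points | 0.0454 | 71.1% |
| 5% | 5.8 points | 0.0445 | 72.7% |
| 10% | 8.2 points | 0.0433 | 74.7% |

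As one concrete case, take hospital rates of 85, 88, 92, 95, 97 and 98% (assumed). The mean is 92.5% and the between-hospital variance 0.0022. The share is 0.0022 / (0.925 × 0.075) = 0.0022 / 0.0694 = 3.2%, which gives power of about 72%.

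**Step 3: true level of the unadjusted tests.** If allocation is balanced within hospital, the treatment contrast has true variance (1 − h) times what the unadjusted test assumes. The two-sided type I error is P(|Z| > 1.96 / √(1 − h)):
- h = 1%: 0.049
- h = 5%: 0.044
- h = 10%: 0.039

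**Step 4: sparseness for fusion.** Expected non-unions: 130 × 0.073 = 9.5. Spread over 6 × 2 = 12 hospital-by-arm cells, that is about 0.8 per cell, so some strata may have none.

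**Step 5: the pre-operative score.** Compared with a model of follow-up scores that leaves baseline out, using baseline as a covariate multiplies the variance by (1 − ρ²):
- ρ = 0.3: 0.91, so 130 patients act like 130 / 0.91 = 143
- ρ = 0.5: 0.75, so 130 patients act like 130 / 0.75 = 173

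For the week-52 contrast, a repeated-measures model with baseline as one of the responses and a common baseline mean gives the same ratios, 0.91 and 0.75. If each arm has its own baseline mean and the contrast is change from baseline, the ratio is 2(1 − ρ): 1.4 at ρ = 0.3 and 1.0 at ρ = 0.5. How baseline enters therefore matters, as well as whether it does.

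**The case against.** Several points on the other side are sound.

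- **Primary outcome.** A reader might infer that the article plans an unstratified interval for fusion. It does not say so: a hospital-stratified interval fits its wording. Interval method and strata are details that an article commonly leaves to the full protocol or analysis plan. Hospital is unmentioned there, not excluded.
- **Baseline scores.** A reader might infer that the mixed model omits baseline and so loses 9% to 25% of variance. The article gives the model's purpose and class but not its terms. It collects the pre-operative score in the same series as the later visits, so baseline may already be a repeated response. The loss is not shown.
- **Conservatism.** The unadjusted tests are conservative only if allocation is balanced within hospital, for example by blocking, and the article does not state this. Under simple randomisation within hospital, the pooled test keeps its level. If lists are blocked, site balance is already largely secured, so protection against chance imbalance is not a further argument.
- **Cost.** With under one expected non-union per cell, stratifying the fusion comparison brings its own technical choices.
- **Scope.** The chi-square and t tests do not apply to ODI, EQ-5D-5L or VAS.

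After all of this, the core remains: allocation is run by hospital, and the tests that the article does name for the remaining secondary outcomes ignore it.

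**Conclusion.** The point holds, and it is modest. For the outcomes assigned to chi-square and t tests, the stated method does not follow the randomisation. For fusion and the clinical scores, hospital is simply not mentioned. The effect is lost precision of about 1% to 10% of variance for an assumed hospital share of 1% to 10%, with slight conservatism if allocation is balanced within hospital. The comparison is not biased and false-positive claims do not become more likely.

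A baseline gain of 9% to 25% of variance, at assumed correlations of 0.3 to 0.5, arises only if the planned model would otherwise leave baseline out. A reader might also infer that stratifying would rescue the primary test. It would not: power stays at or below 74.7% over the range tried, on the equal-rates assumption. The gap to the stated 90% is a separate sample-size matter.

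**What to change.** Before any unblinded analysis, put the following into the analysis plan.

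1. **Remaining categorical outcomes:** a hospital-stratified Mantel-Haenszel test, in exact form where events are few. **Remaining continuous outcomes:** a linear model with graft and hospital in place of the t test.
2. **Fusion:** a Mantel-Haenszel hospital-stratified risk difference, with an interval method that tolerates strata without non-unions (for example a stratified score interval) and a pre-set rule for pooling small hospitals or those with an empty arm.
3. **ODI, EQ-5D-5L and VAS:** list the model terms: graft, visit, graft-by-visit, hospital and the pre-operative score. The score should enter as a covariate, or as a repeated response with a common baseline mean.
4. **Randomisation:** state whether the hospital lists are blocked, withholding block sizes from sites.

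The cost is wording and a little more analysis work; hospital and pre-operative scores are already collected. The one real downside is sparse strata for fusion, which item 2 addresses.

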### Interventions

Active intervention: rhBMP-2 with HA and local lamina boneControl intervention: the auto-iliac bone graft and local lamina bone

The surgical methods of the active group using rhBMP-2 and the control group using auto-iliac bone graft will be similar except for the procedure of filling the cage in the intervertebral space. TLIF will be routinely performed. Following the posterolateral approach, decompression with foraminotomy and flavectomy will be performed. Total discectomy and endplate preparation will follow. In the active rhBMP-2 group, rhBMP-2 with HA and local lamina bone will be placed in the PEEK cage in the intervertebral body space. Novosis® (CGBio Inc., Gyeonggi-do, Korea), which consists of 0.5 g of HA and 0.5 mg of *E. coli*-derived rhBMP-2, will be used for each segment. In contrast, the control group will receive 5 to 10 cc of auto-iliac bone graft and local lamina bone for each segment. A PEEK cage will be inserted in the intervertebral body space. Percutaneous pedicle screw fixation will be performed at the involved lumbar level. Wound closure will be conducted after drainage.

### Outcome measures

#### Primary outcome

The primary outcome is the interbody union rate at 52 weeks after surgery. The status of the interbody union rate will be evaluated using the ‘bone bridge ratio.’ It will be assessed on coronal and sagittal CT images (1-mm interval cutting image). It is evaluated as the ratio of the bone bridge length to the total length of the upper and lower end plates of the segment. The study will be conducted by two orthopedic surgeons who do not participate in the study.

#### Secondary outcomes

##### Radiographic outcomes

Simple lumbar radiographs, which consist of anterior–posterior, lateral, lateral-flexion and lateral-extension views, will be used to confirm the overall condition of the participant's lumbar spine before surgery. During follow-up, simple radiographs will be obtained to assess for adverse events, such as heterotrophic ossification, cage subsidence, screw loosening, and adjacent segment disease.

